##### Secondary outcomes

Smoking cessation related secondary outcomes at t_3_ and t_4_ will include percentage reduction in CPD, 30-days PPA, repeated PPA, continuous PPA (< 5 cigarettes since target quit date), and urges to smoke (VRS v4-1) [63]. Other secondary outcomes will include perceived stress (Perceived Stress Scale; PSS-10) [64], mindfulness (Freiburg Mindfulness Inventory short version; FFA) [65], smoking self-efficacy (“How confident are you that you will be completely abstinent from smoking cigarettes in one year from now? (1 “not confident at all” -10 “very confident”), and Smoking Self-Efficacy Questionnaire; SEQ-12) [66], subjective health (Short Form Health Survey; SF-12) [67], and life satisfaction (L-1) [68].

The acceptability of the nuumi program will be operationalized as (1) usefulness in quitting smoking ("How helpful do you find the program in not smoking cigarettes?", "To what extent does the program increase your confidence to quit smoking?”), (2) satisfaction with the program ("How would you rate your overall satisfaction with the smoking cessation program?"/"How likely are you to recommend the program to friends or colleagues who want to quit smoking?"), (3) comprehensibility of the content ("How informative did you find the content of the behavioral training?” / "How understandable did you find the content of the behavioral training?”). Usability of the app is also assessed using the System Usability Scale (SUS) [69].

For each questionnaire, the validated German version will be used. If no German version is available, translations will be made by the study staff.

#### Other variables

##### Smoking behavior-related variables

Smoking behavior-related variables include years of smoking, motivation to quit (Motivation To Stop Scale) [70], number and method(s) of previous quit attempts, use of alternative tobacco products and/or ECs, current participation in other smoking cessation program, current use of NRT, and withdrawal symptoms (Wisconsin Smoking Withdrawal Scale; WSWS2-B) [71]. Additionally, EC dependence is queried (Penn State Electronic Cigarette Dependence Index; PSECDI) [72].

##### Adherence and engagement

Adherence is operationalized as (1) self-reported use of the EC (current use and number of days of use), and (2) self-reported engagement with the app (number of daily/weekly uses, number of modules completed, minutes meditated). Participants will be asked whether they participate in any other smoking cessation program in each survey from t_0_ onwards.

##### Subjective evaluation and side effects

Subjective evaluation of the EC and side effects will be measured using items from a variety of scales assessing subjective effects of ECs [12]. Participants will be asked about adverse events in each survey from t_1_ onwards and requested to report all adverse events occurring between the survey time points to the study staff.

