However, although evidence suggests that ECs are likely to be less harmful than combustible cigarettes, they are not without risk, and concerns remain regarding the long-term safety of their usage [17]. While ECs may serve as an effective smoking cessation tool, meta-analysis data shows that approximately 70% of individuals who underwent EC-supported smoking cessation report ongoing EC use at six months or longer [18]. Because the long-term health consequences of ECs use are unknown, EC-supported smoking cessation efforts should include steps to wean individuals who had previously smoked off ECs once smoking cessation has been attained.

In summary, ECs can serve as effective smoking cessation tools by providing individuals with nicotine to suppress withdrawal symptoms. However, individuals undergoing a smoking cessation attempt also suffer from increased affective symptoms such as depressive or anxious mood, irritability, and restlessness [19–21], and factors such as an encounter with other adults who smoke or experiencing stress may further exacerbate the risk of relapse [22, 23]. Thus, to provide adults who smoke with a successful smoking cessation intervention, a program should include components that address the psychological mechanisms of addiction in addition to physical symptoms.

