### Participant timeline

The study will be conducted over a six-month period, during which a total of five surveys will be administered and two interviews will be conducted with a subgroup of participants. Quantitative data collection will take place at t_0_, 4 weeks post-baseline (t_1_), 8 weeks post-baseline (t_2_), 12 weeks post-baseline (t_3_) and 24 weeks post-baseline (t_4_). All participants will receive access to the nuumi intervention directly after t_0_ data collection. Participants will be granted 2 weeks to complete each survey. Primary and secondary outcomes of this study will be answered by analyzing t_3_ and t_4_ data. To minimize fraud potential, survey invitations are personalized and can only be accessed with an individual access key. Surveys can only be completed once by using the individual access key.

Semi-structured interviews will be conducted by research staff with a sub-sample of 15 enrolled participants via videocall or telephone at t_0_ and t_3_. Participants are invited to partake in the baseline survey. Interested participants will indicate their willingness to be invited via email at the end of the baseline survey and will be sent an informed consent form to be signed electronically (Appendix B). The first interview will be conducted within 2 weeks after t_0_, and the second interview within 2 weeks after t_3_. In interview 1, participants will be asked about previous cessation attempts and perceived barriers to smoking cessation, their perceptions, and attitudes towards ECs and towards the use of smartphone apps for smoking cessation. In interview 2, participants will be interviewed about their current smoking and EC use status, their perceptions of the different intervention features, and the perceived effectiveness of the program. Participants may participate in both interviews, however, having participated in the first interview is not a prerequisite for participation in interview 2.

Participant flow and study design are outlined in Fig. 1 in an adapted Consolidated Standards for Reporting Trials (CONSORT-EHEALTH) diagram for pilot and feasibility trials [52, 53].

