##### Other variables

Frequency measures and percentages will be reported for method(s) of previous quit attempts, use of alternative tobacco products and ECs, participation in other smoking cessation programs, NRT use, and EC dependence. Mean and SD will be calculated for years of smoking, motivation to quit, number of previous quit attempts, and withdrawal symptoms. To assess adherence and engagement, frequencies and percentages of current EC use, and number of days of use will be reported. Mean and SD for engagement with the app will be calculated. Further, frequencies and percentages will be reported for the subjective evaluation of the EC, side effects, and adverse events.

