### Strengths and limitations

Several strengths are associated with the present study. To the best of our knowledge, the present study is the first trial to evaluate a smoking cessation program featuring an integrated EC- and app-based behavioral therapy developed based on comprehensive scientific evidence in a real-world setting. Providing data on feasibility, acceptability and initial efficacy may inform further development of similar interventions. The study results will be documented in accordance with international documentation guidelines, including an adapted CONSORT-EHEALTH diagram for pilot and feasibility trials [52, 53].

The research questions of this trial will be assessed using data collected at 12 weeks and 24 weeks post-baseline. This follow-up period is sufficient to detect relapse, as relapse occurs most often during the first few weeks after a quit attempt [78].

Another strength of this study is the mixed-methods approach which allows for a comprehensive understanding of the feasibility and acceptability of nuumi. These insights will contribute to providing a more complete picture of the utility of EC-supported, app-based smoking cessation, which in turn may inform future developments of mHealth-supported EC-based smoking cessation interventions.

We acknowledge that this study design has several limitations. First, as it is designed as a single-arm trial without a control group, the external and internal validity of the results are limited. However, single-arm studies are a common design used to test the feasibility, acceptability, and initial efficacy of new interventions and to pilot study procedures for future RCTs [79].

Although we will not directly compare nuumi with a similar intervention or TAU, descriptive results of initial efficacy, acceptability and user engagement can serve as preliminary indicators of comparability with other smoking cessation interventions. While a sample size of 70 participants does not allow for generalization of findings to a broader population, our sample is larger than those usually included in pilot and feasibility trials [73].

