Informed consent	✓					
Intervention:		✓	✓	✓	✓^a^	
Assessments:						
Participants ‘ characteristics						
Age	✓	✓				
Gender	✓	✓				
Height		✓				
Weight		✓	✓	✓	✓	✓
Pregnancy	✓	✓	✓	✓	✓	✓
Primary outcome						
7-day PPA			✓	✓	✓	✓
Secondary outcomes						
CPD	✓	✓	✓	✓	✓	✓
30-days PPA						
Repeated PPA			✓	✓	✓	✓
Continuous PPA			✓	✓	✓	✓
Urges to smoke		✓	✓	✓	✓	✓
Perceived stress		✓	✓	✓	✓	✓
Mindfulness		✓	✓	✓	✓	✓
Smoking self-efficacy		✓	✓	✓	✓	✓
Subjective health		✓	✓	✓	✓	✓
Life satisfaction		✓	✓	✓	✓	✓
Acceptability		✓	✓	✓	✓	✓
Usability		✓	✓	✓	✓	✓
Adherence			✓	✓	✓	✓
Other variables						
Nicotine dependence		✓	✓	✓	✓	✓
Use of alternative tobacco products	✓	✓	✓	✓	✓	✓
Years of smoking	✓	✓				
Motivation to stop smoking	✓					
Quit attempts and method(s)		✓				
Quit date			✓			
Withdrawal symptoms		✓	✓	✓	✓	✓
EC use	✓	✓	✓	✓	✓	✓
NRT use	✓	✓	✓	✓	✓	✓
Participation in another smoking cessation program	✓	✓	✓	✓	✓	✓
Adverse events			✓	✓	✓	✓
EC dependence			✓	✓	✓	✓
Subjective evaluation and side effects of EC			✓	✓	✓	✓
Dropout			✓	✓	✓	✓
Meditation experience & openness towards meditation		✓				

^a^Participants receive unlimited access to the nuumi app; they can use the nuumi EC as long as they have pods (minimum 12 weeks)

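### Side-effect symptoms are first asked at week 4 and tabulated as plain percentages in a single-arm study, so complaints that smokers already had can be counted as side effects of the e-cigarette

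*Protocol article*

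**What the plan says.** Under *Subjective evaluation and side effects*, the protocol article states: "Subjective evaluation of the EC and side effects will be measured using items from a variety of scales assessing subjective effects of ECs". That section gives no time point for these items. For adverse events it says: "Participants will be asked about adverse events in each survey from t_1_ onwards", and it also asks participants to report events that occur between surveys.

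Table 2 in Appendix A fixes the schedule. The row "Subjective evaluation and side effects of EC" is ticked at t1, t2, t3 and t4 (4, 8, 12 and 24 weeks); the enrollment and baseline cells are empty. The adverse-event row has the same pattern.

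*Participant timeline* sets the start of exposure: "All participants will receive access to the nuumi intervention directly after t_0_ data collection".

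Under *Statistical methods, Other variables*, the planned summary is: "frequencies and percentages will be reported for the subjective evaluation of the EC, side effects, and adverse events". No change from baseline is planned for side effects.

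*Strengths and limitations* concedes that "as it is designed as a single-arm trial without a control group, the external and internal validity of the results are limited". It does not discuss how reported side effects are to be attributed.

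**The concern.** Participants must have smoked at least 5 cigarettes a day for at least 12 months (*Participants*). People with that history may have symptoms such as cough, dry mouth or headache before they start the study e-cigarette. These are my examples; the article does not list the items. With no control arm, each participant's own state before use is the only reference the study could have, and the schedule does not record it for these symptoms.

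The table the plan produces is therefore a prevalence during use. Read as a list of side effects, it can overstate what the device does, because old complaints are counted. It also hides symptoms that improve after switching. This is the first trial of the program, and its stated overall purpose is to prepare procedures for a later randomised trial, so the same schedule could be carried forward.

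This is not a detail that an analysis plan could supply later. The article publishes both the schedule and the summary measure, and a baseline value that was never collected cannot be recovered in the analysis.

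**Working it through.** The protocol states no figure on this point, so there is none to reproduce. The check is a comparison of the schedule with the start of exposure, followed by an illustration of size.

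**Schedule**

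| Item | Before exposure (t0) | t1 to t4 | Source |
|---|---|---|---|
| Subjective evaluation and side effects | no | yes | Table 2 |
| Adverse events | no | yes | Table 2; *Subjective evaluation and side effects* |
| EC dependence | no | yes | Table 2 |
| Withdrawal symptoms (WSWS2-B) | yes | yes | Table 2 |
| Subjective health (SF-12) | yes | yes | Table 2 |

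Access to the program follows directly after t0, so t0 is the only survey before exposure. Side-effect items are asked at 4 of the 5 surveys and at none before exposure. SF-12 is a general health score, not a symptom list. No planned analysis uses SF-12 or WSWS2-B to interpret side effects.

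**Illustration 1: no e-cigarette effect.** Inputs, all assumed: 55 responders (55/70 = 79% of the target sample) and a background prevalence b of 20% or 40%. It is also assumed that everyone with the symptom reports it when asked.

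Expected reports = 55 × b.
- b = 20%: 55 × 0.20 = 11 (Wilson 95% interval 11.6% to 32.4%).
- b = 40%: 55 × 0.40 = 22 (Wilson 95% interval 28.1% to 53.2%).

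The number of new cases is zero in both rows because the scenario assumes it.

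**Illustration 2: some e-cigarette effect.** Inputs: all 70 participants (*Sample size*), an assumed new-onset rate e of 10% among those without the symptom, independent of b, and no symptom resolving.

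Observed prevalence = b + (1 − b) × e. Share of reports that were pre-existing = b / observed. New-onset count = 70 × (1 − b) × e.

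| b (assumed) | Observed | Reports of 70 | New onset of 70 | Pre-existing share |
|---|---|---|---|---|
| 10% | 0.10 + 0.90 × 0.10 = 19% | 13.3 | 6.3 | 53% |
| 20% | 0.20 + 0.80 × 0.10 = 28% | 19.6 | 5.6 | 71% |
| 30% | 0.30 + 0.70 × 0.10 = 37% | 25.9 | 4.9 | 81% |
| 40% | 0.40 + 0.60 × 0.10 = 46% | 32.2 | 4.2 | 87% |

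As b rises, the reported percentage rises while the number of new cases falls. The planned table shows only the reported percentage.

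**The case against.** The strongest objection is that the item wording is not shown. The items come from scales on subjective effects of e-cigarettes, and Table 2 labels the row as side effects of the e-cigarette. If participants are asked what they noticed from using the device, the items have no meaningful answer at t0. This stands for the evaluation items. For symptoms, attributing wording would lessen the problem but not remove it, because a participant with a long-standing cough still has to judge its cause.

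Second, adverse events are collected separately from t1, and collecting them only from the start of exposure is usual practice. This stands as partial cover. A reader might infer that no new or worsened symptom can be identified at all. The documents do not support that, because a participant can report a new event by this route. What is missing is a systematic comparison of the same symptom before and during use.

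Third, quitting itself causes complaints; the Introduction notes that "individuals undergoing a smoking cessation attempt also suffer from increased affective symptoms". A reader might infer that a baseline question would also separate these from device effects. It would not: they arise after t0 and stay confounded with e-cigarette use in a single-arm study. WSWS2-B at t0 to t4 helps in part with withdrawal complaints such as irritability and restlessness.

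Fourth, side effects are a descriptive variable outside the stated objectives, and the article already concedes limited internal validity. Both are true, and they keep the point small.

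Fifth, the change may come late. Recruitment began at the end of October 2023 and completion was expected in June 2024. Counting 24 weeks back from the end of June gives mid-January 2024 as about the latest baseline date, so few or no participants may still be reachable. This stands, and it is why the fix includes a labelling step that needs no new data.

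**Conclusion.** The point holds as a minor, inexpensive improvement. Followed exactly, the plan yields symptom percentages during use that cannot be set against complaints present before use, and there is no comparator to take their place.

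The size is illustrative only. It rests on an assumed background prevalence of 20% to 40%, an assumed 55 responders and full reporting of existing symptoms. Under those assumptions 11 to 22 participants would report a given symptom with no e-cigarette effect. The documents give no symptom prevalence, so no firmer figure is possible.

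Two further inferences are not supported. Side-effect symptoms are not the only measure without a baseline value: adverse events and EC dependence also start at t1, as one would expect of measures that follow exposure. Nor does the article say that the device is untested; *Strengths and limitations* says only that its nicotine delivery has not been tested. The abstinence outcomes are unaffected.

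**What to change.** 1. In *Subjective evaluation and side effects* and in Table 2, add the symptom items, but not the items evaluating the e-cigarette, once at t0. Word them neutrally, without attribution to the e-cigarette, and keep the same wording at t1 to t4.
2. In *Statistical methods, Other variables*, report at each follow-up the number and percentage of participants with a symptom that is new or worse than at t0, beside the raw percentage.
3. For participants without a t0 value, label the table as symptoms reported during follow-up and state that pre-existing symptoms cannot be excluded.
4. State in the limitations that complaints caused by quitting remain confounded with e-cigarette use, and that WSWS2-B addresses this only in part.

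The cost is a slightly longer baseline survey and one extra column in the side-effect table. Participants already enrolled will lack the t0 value. If enrolment has closed, steps 3 and 4 still apply, and steps 1 and 2 can go into the planned randomised trial. Survey length is a weak reason against step 1, since Table 2 already ticks acceptability and usability at baseline, before anyone has used the program.

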##### Nuumi program feature utilization

In addition to the self-reported EC and app utilization data, app feature utilization data of the nuumi program will be collected by the manufacturer of nuumi, Sanos Group GmbH, for the first 8 weeks after program initiation. Using this data, separate secondary analyses will be conducted to investigate the degree to which users engaged with the individual program features, and the relationships between utilization of individual features and smoking abstinence at 4 weeks and 8 weeks post-baseline. Utilization metrics collected by Sanos Group GmbH will include (1) the number of behavioral therapy lessons completed, (2) the number of meditations completed and/or repeated, (3) the number of toolbox exercises completed, (4) the number of times the progress tracking feature was accessed, and (5) the number of days the EC was used.

##### Sample size

Formal sample size calculations are not required for single-arm pilot studies [73]. Target sample size estimation is based on single-arm pilot studies evaluating interventions for smoking cessation [74–76]. In order to address the primary and secondary aims of this trial, and to account for attrition, the target sample size is 70 participants.

### Statistical methods

#### Quantitative data analyses

Analyses will be conducted using the statistical software R, version 4.4.0 (R Core Team, 2024). Given the exploratory nature of this study, data analyses will primarily be descriptive. For categorical variables, frequencies and percentages will be reported. For continuous variables, mean and standard deviation (SD) will be reported. If applicable, statistical comparisons for paired data will be applied to compare scores observed before and after program participation. Statistical significance will be evaluated using a repeated measures two-tailed t-test; the alpha level will be set at 0.05 and a 95% confidence interval will be used. Intention-to-treat (ITT) analyses will be conducted, assuming all individuals not completing a follow-up survey have resumed smoking. In addition, complete cases will be analyzed, i.e. only participants completing the t_3_ and t_4_ survey, respectively, will be included in these analyses. Percentages and patterns of missing data will be assessed using Little’s Missing Completely At Random test and adequate data imputation techniques will be used, if applicable.

##### Primary and secondary outcomes

For the primary outcome, 7-day PPA at t_3_ and t_4_, number and percentage of participants self-reporting abstinence will be reported. For the secondary outcomes, measures of frequency and percentages will be reported for 30-days PPA, repeated PPA and continuous PPA, and measures of central tendency will be reported for CPD and urges to smoke. Paired t-tests will be conducted to assess changes in CPD and urges to smoke from t_0_ to t_3_ and from t_0_ to t_4_. Mean and SD will be reported for perceived stress, mindfulness, smoking self-efficacy, subjective health and life satisfaction, and paired t-tests will be conducted to assess within-subject changes in these variables. Acceptability outcomes will be reported descriptively.

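### The missing = smoking rule gives no value for CPD, urges or the psychological scores, so their paired t-tests may rest on participants with both values and overstate improvement if dropout is unfavourable

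*Protocol article*

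**What the plan says.** All references are to the protocol article.

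- **Tests.** Under Statistical methods, Primary and secondary outcomes, paired t-tests are planned for CPD and urges from t0 to t3 and from t0 to t4. For stress, mindfulness, self-efficacy, subjective health and life satisfaction, "paired t-tests will be conducted to assess within-subject changes in these variables". No analysis set is named for any of these tests. The general rule is "Statistical significance will be evaluated using a repeated measures two-tailed t-test; the alpha level will be set at 0.05".
- **Intention-to-treat rule.** Quantitative data analyses plans ITT analyses "assuming all individuals not completing a follow-up survey have resumed smoking".
- **Complete cases.** The same paragraph continues: "In addition, complete cases will be analyzed", meaning those who completed the t3 or the t4 survey.
- **Imputation.** Missing-data patterns are to be examined with Little's MCAR test, and "adequate data imputation techniques will be used, if applicable". The outcomes, method and condition are not given.
- **Sample size.** "Formal sample size calculations are not required for single-arm pilot studies"; "the target sample size is 70 participants", chosen partly "to account for attrition". No attrition rate is stated.
- **Data collected.** Table 2 in Appendix A schedules CPD, urges and every psychological scale at t0, t1, t2, t3 and t4. Data collection, management, and monitoring lets participants skip any question, so scores can also be missing among survey completers.

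**The concern.** Recoding a non-responder as a smoker settles abstinence. It does not settle a stress score, an urge rating or a number of cigarettes. For these outcomes the announced ITT analysis therefore cannot be carried out from the stated rule, and the complete-case analysis, presented as an addition, is the only one that is fully defined.

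Within-group change in these outcomes is a stated secondary objective, and the paired t-tests are its only planned significance tests. There is no control arm, so an improvement produced by losing the people who did badly looks the same as a benefit of the programme. The plan already presumes that non-completers did badly, because it counts them as smokers. A default to completers would treat the same people as ignorable for urges and CPD. The week 4 and week 8 scores show how later dropouts were doing before they left, yet a two-point paired test cannot use them. Inflated changes would then feed into the planned RCT.

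**Working it through.** **Inputs.** From the protocol: 70 enrolled, one arm, two-sided alpha 0.05, five visits. Not in the protocol and therefore assumed: attrition *d*, and how non-completers differ from completers. The figure of 70 cannot be reproduced, because no effect size, SD, power or dropout rate is given.

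**Step 1: what the ITT rule supplies.**

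| Outcome | Value under missing = resumed smoking |
|---|---|
| 7-day abstinence | not abstinent |
| CPD | smoking, but no count |
| Urges, stress, mindfulness, self-efficacy, subjective health, life satisfaction | none |

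**Step 2: non-completers back at baseline.** If their change is 0, the mean change in all 70 is (1 − d) × completer mean change. The completer figure is then too large by the factor 1/(1 − d): 1.25 at d = 20%, 1.43 at 30%, 1.67 at 40%. A completer change of 0.50 SD corresponds to 0.40, 0.35 and 0.30 SD in all 70.

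**Step 3: no true change overall.** Let non-completers be worse than completers by *g* SD of the change score, with mean change 0 in all 70. Then (1 − d)·m + d·(m − g) = 0, so the completer mean is m = d × g. The chance that the completer t-test declares a benefit (nominal 2.5% in that direction) is:

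| d | pairs | g = 0 | g = 0.25: bias, false benefit | g = 0.5: bias, false benefit |
|---|---|---|---|---|
| 20% | 56 | 2.5% | 0.05, 5.5% | 0.10, 11% |
| 30% | 49 | 2.5% | 0.075, 7.6% | 0.15, 18% |
| 40% | 42 | 2.5% | 0.10, 9.2% | 0.20, 24% |

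For scale, the change detectable with 80% power is 0.34 SD with 70 pairs and 0.41 SD with 49.

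**Step 4: five-visit simulation.** N = 70, normal scores, correlation 0.6 between visits, true change zero, and people who drop out do not return. Bias here is in SD of the score, in the direction of benefit. One SD of the change is √(2 × (1 − 0.6)) = 0.89 of that unit. The likelihood estimate uses all visits.

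| Dropout depends on | Attrition | Completer bias | Likelihood bias |
|---|---|---|---|
| nothing (MCAR) | 25% | 0 | 0 |
| last observed change | 25–33% | 0.06–0.17 | essentially 0 |
| current, unobserved change | 26%, 29%, 30% | 0.07, 0.14, 0.20 | 0.03, 0.07, 0.11 |

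In the second row the completer t-test rejects in 7–27% of trials; under MCAR it rejects in 5%. In the third row the likelihood estimate keeps 0.03/0.07 = 43%, 0.07/0.14 = 50% and 0.11/0.20 = 55% of the bias, that is, about half. The ranges come from varying the assumed dropout intercept and slope.

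**The case against.** Four stronger readings are tempting, and the document supports none of them.

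- **That the tests are stated to use completers only.** A reader might infer this from the choice of test. No analysis set is named, complete cases are an additional analysis, and imputation is foreseen. Restriction to pairs follows only if nothing is imputed.
- **That Little's test chooses the method.** The test and the imputation stand in one sentence, but no rule links the result of the first to use of the second.
- **That the results will be biased towards benefit.** This requires dropout related to outcome. Under MCAR there is no bias, and the document gives neither an attrition rate nor a dropout pattern.
- **That a mixed model removes the problem.** It does so where dropout depends on observed scores, and the second row of Step 4 assumes exactly that. If relapse comes first and non-response follows, about half the bias can remain.

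It can also be said that imputation detail belongs in an analysis plan that is not shown, that the study is exploratory and mainly descriptive, that the article concedes limited internal validity, and that abstinence, the primary outcome, has a clear rule. All of this is fair and lowers the weight. It does not dispose of the point, because the article itself names the test and the ITT rule. That rule cannot apply to these outcomes, and that test leaves two scheduled visits unused.

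**Conclusion.** The point holds as a conditional one. For CPD, urges and the psychological scores, the stated ITT rule defines no value, the imputation is left open, and the named test uses two of the five visits. If the tests default to participants with both values and dropout is unfavourable, as the plan's own rule presumes, improvement is overstated. An illustrative size is 0.06–0.17 SD at 25–33% attrition, with 7–27% rejection under no true change. These figures rest on the assumed attrition, the correlation of 0.6 and the assumed dropout mechanism. In the scenarios examined the likelihood analysis was never worse than the completer test, though not always unbiased. The severity is moderate: the outcomes are secondary and exploratory, and the abstinence results are untouched.

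**What to change.** 1. Make the main analysis of CPD, urges and the psychological scores a linear mixed model for repeated measures, with t0 to t4 as categorical visits and all enrolled participants included. Report the t3 − t0 and t4 − t0 contrasts with 95% confidence intervals.
2. Keep the paired t-tests in completers as a sensitivity analysis, labelled as such.
3. For CPD, add a sensitivity analysis that sets missing values to baseline CPD, which carries the missing = smoking assumption over to the count.
4. State that the missing = smoking rule applies to abstinence outcomes, and that the choice of method for the other outcomes does not depend on the result of Little's test.
5. State that the model assumes data missing at random and corrects only for dropout explained by observed scores.

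The cost is revised wording and a little more analysis in R. No new data are needed, because Table 2 already schedules every scale at all five visits. The price is the missing-at-random assumption, which should be stated with the results.
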